### Specific aims:

1. To determine the incidence of NVAF diagnosis in England from the year 2009 to 2019.
2. To determine the proportions of patients with NVAF and those with NVAF and cancer who were prescribed OACs, antiplatelet alone or no treatment.
3. To examine the temporal trends of prescribing different types of OACs (i.e. VKAs and NOACs), and assess the factors associated with not prescribing OACs including patient demographics, socioeconomic status, history of cancer and other comorbidities, stroke and bleeding risk.
4. To assess the effect of OACs prescribing vs. no OACs on the clinical outcomes (stroke, bleeding, and death) in a comparative cohort of NVAF patients eligible for anticoagulation after controlling for patients' comorbid conditions, frailty, age, and antiplatelets use.
5. To assess the rate of clinical outcomes (i.e. bleeding recurrence, stroke, and mortality) after MB events and how they relate to OACs resumption and the timing of restarting OACs after the MB event.
6. To explore the variability across patient groups regarding OACs resumption after MB events and whether patients have continued on the same OAC before the MB event, switched to another OACs or received lone antiplatelet therapy.
7. To assess and compare patients' risk for stroke and bleeding recurrence using HAS-BLED, CHA2DS2-VASC, HEMORR?HAGES and GARFIELD-AF risk assessment scores, at the time of the indexed major bleeding event.

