**Covariates:**

- Patients' demographic information (age, gender, ethnicity, body mass index (BMI), geographic location (rural vs. urban), smoking status, alcohol consumption, Charlson comorbidity index for the severity of comorbidity (Appendix 3 and 4), electronic frailty index (eFI), and the index of multiple deprivation (IMD).
- Clinical covariates such as CHA2DS2-VASc, GARFIELD-AF, HAS-BLED, and HEMORR2HAGES risk assessment scores all at the time of the index haemorrhage event.

- Anatomic location of the index MB event will be identified and classified according to the critical site of bleeding (i.e., intraspinal, intracranial, intraocular, intra-articular, pericardial or other bleeding sites).

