2. Phase 2 – Comparative study: For comparison of demographic variables and comorbidities among OACs treated and not treated individuals, independent sample t tests will be used for numeric variables, while Chi squared  $\chi^2$  tests or Fisher exact tests will be used for categorical variables. To control for imbalances in patient characteristics between cohorts, we will calculate an exposure-specific propensity score as the predicted probability of receiving OACs conditional upon individuals baseline covariate (as described in section M) using logistic regression models. Then we will consider applying propensity score matching methods to match each OACs unexposed controls to up to 5 NVAF OACs exposed cases using a calliper of 0.2 standard deviation (SD) of the propensity score logit. After matching, Cox regression will be used to compute hazard ratios (HRs) of the outcomes of interest, comparing exposure to OACs versus no OACs. Initially crude HRs will be obtained, then stratified by type of OACs (i.e., VKAs and NOACs) and adjusted for age, and other important covariates described in section N. In this phase immortal time bias would occur due to the definition of exposure, where in the time from AF diagnosis till receipt of OACs those in the “OACs prescribed group” cannot have the outcome by design, otherwise they would have been classified as non OAC users. To avoid the problem of immortal time bias, we will consider using time-varying exposures, where in a survival analysis, the time period previous to the index date of OACs initiation is reclassified as nonuser for those in the “OACs prescribed group”.

3. Phase 3 – Major bleeding events cohort: At first, we will use descriptive statistics to present the overall characteristics of this cohort who have experienced major bleeding events while taking OACs. After that patients will be divided to 2 groups one for the patients who resumed anticoagulation after the index major bleeding event and the other for the group who remained OACs free and will compare the patient characteristics between the two groups using Chi squared  $\chi^2$  tests, Fisher's exact tests, and analysis of variance, as appropriate. Survival (time-to-event) models will be constructed to compare the time between the indexed major bleeding to the earliest event of stroke, bleeding, or all-cause mortality considering if patients were restarted on OACs or not. In Cox models we will control for age, time to OACs resumption, CHA2DS2-VASc

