score and HAS-BLED score, Charlson comorbidity index, and eFI. In a secondary analysis, we will group patients who resumed OACs according to the type of anticoagulation drug used after the indexed bleeding events and compare the outcomes using Cox models in a similar manner. We will assess the proportional hazards assumption by examining Schoenfeld residuals and confirming that it is not violated. To identify variables independently associated with resuming

OACs after the indexed bleeding event multivariate logistic regression models will be used and fitted with the covariates described in section N. All the statistical analyses will be carried out using STATA (version 16).

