### **Plan for addressing confounding**

In phase 2, we aim to conduct a comparison between NVAF patients who were exposed to OACs (cases) and patients who were not exposed to OACs (controls). We will calculate an exposure-specific propensity score as the predicted probability of receiving OACs conditional upon the effect of potential confounders (described in section M). Then we will use a propensity score matching method to achieve similarity of measured confounders across cases and control groups. When estimating HRs using Cox regression models for the outcomes of interest among patient groups, we will also adjust for age, sex, IMD, stroke risk, bleeding risk, frailty, Charlson comorbidity index, and prescription of antiplatelets.

In phase 3, when looking at the predictors of restarting OACs after the indexed bleeding events we will take in account many confounders that could influence this decision, this will be done by using a multinomial logistic regression to adjust for the covariates described in section N. These covariates will also be considered when conducting survival analysis to compare the time between the indexed major bleeding to the earliest event of stroke, bleeding, or death among patients who restarted OACs and those who did not. Also, when evaluating the outcomes of restarting OACs we will consider the timing of restarting anticoagulation after bleeding, and stratify patients based on different time periods of OACs reinitiating.

In both phase 2 and 3, an additional analysis will be considered to assess the robustness of results to unmeasured confounding using the E-value methodology. This estimates what the relative risk would have to be for any unmeasured confounder to overcome the observed association of OACs prescribing with the clinical outcomes of stroke, bleeding, or mortality.

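### The Phase 3 comparison of anticoagulant types after a bleed does not account for the type taken at the bleed, although the protocol already derives it

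*Protocol*

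**What the plan says.** The Phase 3 part of Data/statistical analysis first compares patients who resumed an OAC after the index major bleed with those who did not. The covariates are listed in one sentence: "In Cox models we will control for age, time to OACs resumption, CHA2DS2-VASc" "score and HAS-BLED score, Charlson comorbidity index, and eFI". The secondary analysis is then restricted to resumers: "we will group patients who resumed OACs according to the type of anticoagulation drug used after the indexed bleeding events", and the plan is to "compare the outcomes using Cox models in a similar manner".

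The Phase 3 covariate list (under Exposures, outcomes and covariates) holds demographic and lifestyle factors, the Charlson index, the frailty index and deprivation. It adds the four "risk assessment scores all at the time of the index haemorrhage event" and the bleed site: "Anatomic location of the index MB event will be identified and classified according to the critical site of bleeding".

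Plan for addressing confounding refers back to section N for the Phase 3 models and says: "These covariates will also be considered when conducting survival analysis". It adds stratification by time to restart.

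The drug taken before the bleed appears elsewhere, as part of an outcome. Aim 6 asks "whether patients have continued on the same OAC before the MB event, switched to another OACs or received lone antiplatelet therapy", and the Phase 3 outcomes repeat this.

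**The concern.** Phase 3 patients come from the OAC-exposed group of Phase 2, whose members were on either a VKA or a NOAC, so the drug taken before the bleed varies. Resumers on a NOAC after the bleed include patients who were already on one and patients moved from a VKA on which they had bled. Resumers on a VKA are a mixture of the mirror-image kind. Post-bleed type is tied to pre-bleed type by construction, since staying and switching are defined relative to it.

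If pre-bleed type, or the fact of switching, carries prognostic information beyond the listed covariates, a hazard ratio by post-bleed type picks it up. Readers would probably take that ratio as a comparison of drugs, and Study type describes Phase 3 as hypothesis testing. The resumption model has a related gap: as its covariates stand, the drug at the bleed is not among the named predictors of restarting.

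**Working it through.** **Text check.** Each place that fixes the Phase 3 grouping or adjustment was read for the OAC type before the bleed.

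| Place in the protocol | What it fixes | Pre-bleed OAC type named? |
|---|---|---|
| Data/statistical analysis, Phase 3 Cox models | age, time to resumption, CHA2DS2-VASc, HAS-BLED, Charlson, frailty | No |
| Same section, secondary analysis | groups by post-bleed type, resumers only | No |
| Same section, resumption model | section N covariates | No |
| Phase 3 covariate list | demographics, Charlson, frailty, deprivation, four scores, bleed site | No |
| Plan for addressing confounding, Phase 3 | section N covariates, strata by time to restart | No |
| Aim 6 and Phase 3 outcomes | same drug, switched or lone antiplatelet | Yes, as an outcome only |

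The variable will therefore be derived, but no stated model uses it.

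**Illustration of size.** The protocol gives no figure to reproduce, and every input here is an assumption. Suppose that among resumers 60% bled on a VKA and 40% on a NOAC, that 60% of the VKA bleeders resume on a VKA, and that 90% of the NOAC bleeders resume on a NOAC.

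- VKA to VKA: 0.60 × 0.60 = 0.36
- VKA to NOAC: 0.60 × 0.40 = 0.24
- NOAC to NOAC: 0.40 × 0.90 = 0.36
- NOAC to VKA: 0.40 × 0.10 = 0.04

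Pre-bleed VKA use is then 0.36 / (0.36 + 0.04) = 90% in the post-bleed VKA group and 0.24 / (0.24 + 0.36) = 40% in the post-bleed NOAC group.

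Let h be the hazard of pre-bleed VKA users relative to pre-bleed NOAC users that remains after the stated adjustment. Let the post-bleed drug have no effect. The apparent NOAC versus VKA ratio, taken as a ratio of group-average hazards, is

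(0.40h + 0.60) / (0.90h + 0.10)

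- h = 1.25: 1.100 / 1.225 = 0.90
- h = 1.5: 1.200 / 1.450 = 0.83
- h = 2.0: 1.400 / 1.900 = 0.74

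**Wider shares.** Let 20% to 60% of the post-bleed NOAC group have been on a VKA before, and 5% to 10% of the post-bleed VKA group on a NOAC before. The ranges become 0.85 to 0.94 (h = 1.25), 0.75 to 0.90 (h = 1.5) and 0.62 to 0.84 (h = 2.0).

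**Switching alone.** Suppose instead that pre-bleed type does not matter but switching multiplies the hazard by s. With f and g the shares of switchers in the post-bleed NOAC and VKA groups, the apparent ratio is (f·s + 1 − f) / (g·s + 1 − g). At f = 0.60 and g = 0.05:

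- s = 0.7: (0.42 + 0.40) / (0.035 + 0.95) = 0.820 / 0.985 = 0.83
- s = 1.5: (0.90 + 0.40) / (0.075 + 0.95) = 1.300 / 1.025 = 1.27

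The true ratio is 1.00 in every case, and the apparent ratio can fall on either side of it.

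**The case against.** The strongest reply is that this is one sentence about a secondary analysis, that the clinical covariates are introduced with open wording, and that exact model terms are commonly settled in a statistical analysis plan. No passage excludes pre-bleed type. The reply limits the weight of the point. It does not remove it, because the protocol itself fixes the grouping and writes out the Cox covariates, and following them as written gives the mixed comparison.

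The confounding plan also brings the section N covariates, including bleed site, into the survival models. To the extent that pre-bleed drug acts through the site of the bleed, that path is partly covered. Any h in the illustration would have to remain after these adjustments, and nothing in the protocol supports a particular value. The E-value analysis does not fill the gap, since it addresses unmeasured confounding and this variable is measured.

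A reader might infer two stronger claims that the protocol does not support:

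- **That antiplatelet or NSAID use is absent from Phase 3 adjustment.** The Phase 3 list does not repeat the separate drug lists of Phases 1 and 2. But HAS-BLED has a drugs/alcohol item and GARFIELD-AF includes antiplatelet use, and both are measured at the index bleed. Neither score, as described, contains OAC type.
- **That Aim 6 cannot be answered.** It is exploratory, and the Phase 3 outcomes serve it directly by describing who stayed on the same drug, switched or moved to lone antiplatelet therapy. It does not depend on a Cox covariate.

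**Conclusion.** The point stands in limited form. The comparison of outcomes by post-bleed OAC type does not condition on the type taken at the bleed, so its hazard ratio cannot separate drug type from switching and pre-bleed drug history. The resumption model likewise does not name that type as a predictor.

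The size and direction of any bias are unknown. The values 0.90 to 0.74 rest wholly on the assumed 60%, 60% and 90% shares and a residual hazard ratio of 1.25 to 2.0. They show that the effect could be material, not that it will be. The secondary comparison by type is at issue, and the point does not show that the main resumed versus not-resumed comparison is biased. It should be corrected because the remedy is cheap and the variable will already be in hand.

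**What to change.** 1. Add OAC type at the index bleed (VKA or NOAC) to the Phase 3 covariate list, the resumption model and the Phase 3 Cox models.
2. In the secondary analysis, compare post-bleed types within pre-bleed type. Alternatively, report the before-to-after pairs (VKA to VKA, VKA to NOAC, NOAC to the same NOAC, NOAC to another OAC), with a rule set in advance for pooling small cells.

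**Cost.** A wording change and a few more model terms, with no new data, because Aim 6 already needs the same prescriptions. Some cells will be sparse: in the illustration the NOAC to VKA group is 4% of resumers, or 40 per 1,000. Estimates within pre-bleed type will be less precise than a pooled ratio, and some pairs may be suitable for description only.

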### **Plan for addressing confounding**

In phase 2, we aim to conduct a comparison between NVAF patients who were exposed to OACs (cases) and patients who were not exposed to OACs (controls). We will calculate an exposure-specific propensity score as the predicted probability of receiving OACs conditional upon the effect of potential confounders (described in section M). Then we will use a propensity score matching method to achieve similarity of measured confounders across cases and control groups. When estimating HRs using Cox regression models for the outcomes of interest among patient groups, we will also adjust for age, sex, IMD, stroke risk, bleeding risk, frailty, Charlson comorbidity index, and prescription of antiplatelets.

In phase 3, when looking at the predictors of restarting OACs after the indexed bleeding events we will take in account many confounders that could influence this decision, this will be done by using a multinomial logistic regression to adjust for the covariates described in section N. These covariates will also be considered when conducting survival analysis to compare the time between the indexed major bleeding to the earliest event of stroke, bleeding, or death among patients who restarted OACs and those who did not. Also, when evaluating the outcomes of restarting OACs we will consider the timing of restarting anticoagulation after bleeding, and stratify patients based on different time periods of OACs reinitiating.

In both phase 2 and 3, an additional analysis will be considered to assess the robustness of results to unmeasured confounding using the E-value methodology. This estimates what the relative risk would have to be for any unmeasured confounder to overcome the observed association of OACs prescribing with the clinical outcomes of stroke, bleeding, or mortality.

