According to previous studies, elderly patients (>85 years) are less likely to be prescribed anticoagulation therapy, this observation is well documented in several studies, and is mainly attributed to the overestimation of bleeding risk. Moreover, elderly patients with high risk for stroke and those with coronary artery disease are more likely to be prescribed only one antiplatelet therapy, despite the 2016 ESC guidance which state that antiplatelet monotherapy should not be used for stroke prevention in AF patients. Observational studies showed that under prescribing of OACs in high-risk AF patients is associated with higher rates of stroke rates and death. OACs prescribing is largely based on physician's assessment of benefit (reducing stroke risk) versus risk (potential for bleeding), while considering many patients related factors. An example to this, is patients with AF and cancer since their risks of venous thromboembolism (VTE) and of non-cardio embolic stroke are higher than in the general population and may have to factor into the decision for some cancer subtypes, and also the bleeding risk is often much higher in patients with cancer due to coagulopathies, thrombocytopenia, anaemia that increase the propensity towards bleeding events. This illustrates the risk–treatment paradox previously reported in AF management that patients at higher risk of stroke and who are more likely to benefit from OACs are not receiving appropriate treatment, due to their bleeding risk. A comparative evaluation of physicians' decisions to prescribe OACs or not in high risk AF patients and their associated clinical outcomes could yield more informative, actionable conclusions if it provides a focused evaluation of patients characteristics and co-morbidities to identify the type of high-risk AF patients who would benefit from OACs without experiencing bleeding events.

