Earlier studies have shown that anticoagulation therapy based on guideline risk stratifications is associated with a 60%–70% reduction in thromboembolic events and mortality. However, there is still room to improve risk stratification of patients with AF and anticoagulation. Recently, the Global Anticoagulant Registry in the FIELD-Atrial Fibrillation (GARFIELD-AF) model was developed and it allows the simultaneous prediction of stroke, bleeding, and mortality. This model is not a risk score that categorizes patients into risk groups, but instead it provides a risk prediction on a continuous scale. After external validation of the model in a Danish cohort, the GARFIELD-AF model was superior to CHA2DS2-VASc in predicting stroke/SE and comparable with HAS-BLED for predicting major bleeding. Due to the novelty of this risk prediction tool, further studies are needed to demonstrate its ability to accurately stratify AF patients based on their risk of stroke, bleeding, and mortality to promote informed decision-making to prescribe OACs.

Another contributing factor to the under-prescription of OACs in AF patients is history of major bleeding events during anticoagulation therapy. A meta-analysis of observational studies that evaluated the effect of reinitiating OACs on bleeding recurrence and thromboembolic events found a reduction in the risk of thromboembolism and all-cause mortality, without increasing recurrence of bleeding. Since randomized controlled trials (RCTs) that tested OACs, have excluded patients with previous intracranial haemorrhage (ICH), the timing to reinitiate OACs after ICH has not been systemically studied, and varies widely in observational studies from (72 hr to 30 weeks) reflecting lack of consensus. Moreover, of the available bleeding risk scores, the HAS-BLED score has been validated to predict ICH and recurrent ICH after first spontaneous ICH. However, it remains unclear if other risk assessment scores for stroke and bleeding hold similarly in these high-risk individuals and if they could be used to inform

decision-making for reinitiating OACs in these patients.

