The available evidence presents several key aspects of AF management and the challenges associated with OACs prescribing in this population. There are still limitations in studies addressing the under-prescription of OACs in AF patients including patients with history of major bleeding events. In this proposed study we first aim to explore the incidence of NVAF in England to assess patients' characteristics and predictors of OACs prescribing in patients with NVAF in general and in those who have cancer as well. By examining the characteristics of NVAF patients who are less likely to receive a prescription for OACs, we will be able to further evaluate and compare the clinical outcomes of this sub-group of patients with a similar cohort of AF patients treated with OACs. Results could help determine in which AF patients at risk for stroke, OACs can be safely prescribed, taking in account patients' comorbidities, stroke and bleeding risk profiles. In addition to that, by looking separately at patients with history of major bleeding due to OACs, we

aim to evaluate the timing of reinitiating OACs and if stroke and bleeding risk assessment using the available risk prediction scores could be used to inform decision-making for reinitiating OACs in these patients, and their clinical outcomes.

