## Limitations of study design

Data on patient characteristics and other covariates included in this study may not be fully complete in CPRD. One of the foremost limitations of this analysis was that we will not be able to calculate a full HAS-BLED and HEMORR2HAGES scores for each patient, and therefore fully ascertain bleeding risk, (as a high risk of bleeding may have led to an anticoagulant not being prescribed). Imputation methods will be explored and applied to minimize the impact of the missing data. Sensitivity analysis will also be carried to investigate the effect of the missing data on the results of the analysis, these includes alcohol consumption and labile INR for the calculation of HAS-BLED, and genetic factors included in the HEMORR2HAGES score. Due to the retrospective nature of the study, data on adherence to OACs may not be well recorded and difficult to assess. Also, we might not be able to capture the exact timing of reinitiating OACs after MB events, since some patients might resume anticoagulation in hospital settings and such information will not be available through HES APC linkage.

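### For bleeding, the planned E-value tests only movement to the null, so it cannot show whether a bleeding hazard ratio near or modestly above 1 is robust to the confounding that can be inferred from the plan

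*Protocol*

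**What the plan says.** In the Protocol, Plan for addressing confounding, the proposal for Phases 2 and 3 is that "an additional analysis will be considered to assess the robustness of results to unmeasured confounding using the E-value methodology". The next sentence says what the method is to answer: "This estimates what the relative risk would have to be for any unmeasured confounder to overcome the observed association of OACs prescribing". It applies this "with the clinical outcomes of stroke, bleeding, or mortality", with no difference between outcomes and no mention of the direction of bias.

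Limitations of study design concedes that "we will not be able to calculate a full HAS-BLED and HEMORR2HAGES scores for each patient, and therefore fully ascertain bleeding risk", and explains why this matters: "as a high risk of bleeding may have led to an anticoagulant not being prescribed". Study background describes the same pattern of prescribing: higher-risk patients "are not receiving appropriate treatment, due to their bleeding risk".

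Two further statements in Study background bear on how a bleeding result would be used. Earlier evidence on restarting OACs after a major bleed is summarised as benefit "without increasing recurrence of bleeding". The stated hope for this study is: "Results could help determine in which AF patients at risk for stroke, OACs can be safely prescribed".

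**The concern.** An E-value directed at the null is informative when the worry is that confounding produced the observed association. For stroke and mortality, where OACs are expected to look protective, that is the right worry: healthier patients may have been the ones treated.

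For bleeding, the confounder that the protocol describes works the other way. If unmeasured bleeding risk makes prescribing less likely, it is more common among the untreated. It also raises their bleeding rate, and so pulls the OAC-versus-none HR down. When the observed HR is at or a little above 1, the question that matters is how much harm this could be hiding. The planned E-value instead asks how strong a confounder that is more common among the treated would have to be to produce the small excess seen.

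At stake is the reading of a near-null bleeding result. The planned figure would be close to 1 in that case. It would tell the reader nothing about masked harm, and could be taken to mean that the small excess is fragile when the plausible bias runs in the other direction.

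**Working it through.** **Inputs from the protocol.** The contrast is an HR for OAC versus no OAC (Data/statistical analysis, Phase 2). The E-value is defined as movement to the null. Residual bleeding risk is acknowledged. The protocol gives no bleeding HR, no confounder strength and no E-value, so there is no figure of the plan's own to reproduce. The values below are assumptions for illustration: observed HR 0.8 to 1.2, and confounder relative risks of 1.5, 2 and 3. The HR is treated as an approximate risk ratio.

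**Step 1: direction.** Let U be unmeasured bleeding risk. U makes OAC use less likely and bleeding more likely. Both effects lower the OAC bleeding HR, so the true HR lies above the observed one.

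**Step 2: the planned E-value.** E = RR + √(RR × (RR − 1)), with 1/RR used when RR is below 1.
- HR 1.0: 1.0 + √0 = 1.00
- HR 1.1: 1.1 + √(1.1 × 0.1) = 1.1 + 0.33 = 1.43
- HR 1.2: 1.2 + √(1.2 × 0.2) = 1.2 + 0.49 = 1.69
- HR 0.8: 1/0.8 = 1.25, and 1.25 + √(1.25 × 0.25) = 1.81

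For HRs above 1, these values describe a confounder that pushed the HR up. For 0.8, the value describes one that pushed it down, which is the relevant direction.

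**Step 3: how much could be masked.** With the same relative risk R on both links, the bounding factor is B = R²/(2R − 1). The largest compatible true HR is observed HR × B.

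| R on both links | B | Observed 1.0 | Observed 1.1 | Observed 1.2 |
|---|---|---|---|---|
| 1.5 | 2.25/2 = 1.125 | 1.12 | 1.24 | 1.35 |
| 2 | 4/3 = 1.33 | 1.33 | 1.47 | 1.60 |
| 3 | 9/5 = 1.80 | 1.80 | 1.98 | 2.16 |

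An observed 0.8 with R = 2 is compatible with up to 0.8 × 1.333 = 1.07.

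**Step 4: the informative figure.** Apply the E-value formula to T/HR, where T is a harm value. With an illustrative T = 1.5:
- Observed 1.0: ratio 1.50, strength 2.37
- Observed 1.1: ratio 1.364, strength 1.364 + √(1.364 × 0.364) = 2.07
- Observed 1.2: ratio 1.25, strength 1.81

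**Step 5: comparison.** As the observed HR goes from 1.0 to 1.2, the planned figure rises (1.00, 1.43, 1.69) while the strength needed to mask 1.5 falls (2.37, 2.07, 1.81). The planned figure cannot stand in for the other.

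**The case against.** Several points on the other side are sound, and they limit the claim.

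- **The plan does not state a direction of bias.** A reader might infer that the protocol admits its confounding hides bleeding harm. It does not. It says that bleeding risk is incompletely measured and may have affected prescribing; the downward bias is a deduction from that. The protocol also attributes under-prescribing in the elderly mainly to overestimated bleeding risk, and channelling on a misjudged risk confounds less than channelling on true risk.
- **The E-value is not tied to a safety claim.** A reader might infer that the hope about safe prescribing rests on this analysis. That hope stands in Study background, while the E-value is an additional analysis that is only to be considered.
- **It is not the only relevant check.** Limitations of study design also plans sensitivity analyses for alcohol consumption, labile INR and genetic factors in the bleeding scores. These address the named gaps, but do not ask how much harm other residual confounding could conceal.
- **Much bleeding risk is measured.** The propensity model includes bleeding history, anaemia, kidney and liver disease, fall risk, malignancy, alcohol abuse, antiplatelets and NSAIDs. The Cox models add bleeding risk, frailty and the Charlson index. A residual confounder with relative risks of 2 or 3 on both links, beyond all of these, is an assumption.
- **The problem depends on the result.** Below 1 the planned E-value points the right way. Clearly above 1 the study would report harm anyway, and the E-value would still answer a valid question about upward confounding. The cited near-null evidence concerns restarting after a bleed, so it bears on Phase 3 more than on Phase 2.
- **The detail could sit in a statistical analysis plan.** A non-null target is the kind of detail often put there, and nothing in the protocol excludes one. But the protocol does state which question the E-value is to answer, and gives the same one for bleeding as for stroke.

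**Conclusion.** The point holds in a limited form, as a cheap improvement. The E-value as described suits stroke, mortality and a bleeding HR below 1. For a bleeding HR near or modestly above 1 it addresses only upward confounding, and cannot show whether the result withstands the downward confounding that the protocol's own limitations imply.

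The size is conditional. At an observed HR of 1.1 the planned figure is 1.43 whatever is masked, while the true HR could be up to 1.24, 1.47 or 1.98 for confounder relative risks of 1.5, 2 or 3 on both links. This rests on three assumptions: residual bleeding risk remains after the planned adjustment, it lowers the chance of OAC prescribing, and the HR approximates a risk ratio. The bounds are worst cases for the assumed strengths. They are not estimates of the bias in this study, and they do not show that a near-null bleeding result would be wrong.

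**What to change.** In Plan for addressing confounding, keep the usual E-value and add one sentence for major bleeding, clinically relevant non-major bleeding and re-bleeding. It should provide for one or both of the following:

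1. A non-null E-value: the confounder strength needed to move the HR, and its upper confidence limit, up to a harm value that the investigators fix before seeing results. If the upper limit already exceeds that value, report that no confounding is needed.
2. Bias-adjusted HRs over a grid of confounder strengths, in the direction of OACs withheld for bleeding risk.

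This supplements the sensitivity analyses already planned for missing components of the bleeding scores and does not replace them. The calculations are closed-form and need no new data. The one real cost is that a harm value must be named and justified in advance; the 1.5 used above is only an example.
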